### Measurement of secondary outcomes

The secondary outcome is defined as the participant responses to the questionnaire on socioeconomic data, oral hygiene, visits to the dentist, and acceptability of the animation by the pairs mother-child. At the end of T3, the mothers of the experimental group will be asked if the videos were watched at the moment they were sent or if they was watched in other times after the intervention. Question will include how often the videos were watched, which videos they and their children liked the most, and what subject was easier or more difficult to understand and suggestions for improvement. Quality of life will be evaluated using the BOHLAT-P questionnaire [33]. This questionnaire contains 49 questions and is divided into three domains: oral health knowledge, textual understanding, and numerical skills [34]. The mother will answer the BOHLAT-P questionnaire alone, and the researchers will provide help if requested.

### Data management

The data will be collected in standardized dental records identified by numbers (obtained after randomization) for each participant (mother-child). All data will be scanned and stored in a Microsoft Excel spreadsheet for further statistical analysis at the end of the study. Upon completion of the study, data will be made publicly available at the University of Sao Paulo institutional repository.

### Strategies for study retention

During the study period, participants from both groups (control and experimental) will receive a text message informing them of the day and time for the next dental evaluation. In the case of no attendance, calls will be made to the participant (mother) to reschedule the missed dental evaluation.

### Statistical analyses

Data will be analyzed using the GraphPad Prism 8.0 software (GraphPad Software Inc., San Diego, CA, USA). Descriptive analyses, including percentages, means, and standard deviations, will be reported. Answers to the BOHLAP-T questionnaire will be dichotomized into correct and wrong answers. Each correct answer will receive a score of 1, and each wrong answer will receive a score of 0. The maximum and minimum scores are 49 and 0, respectively. The chi-square test will be used to analyze categorical variables, the Mann-Whitney test will be used to compare the inter-group differences, and Friedman test will be used to calculate intra-group differences in relation to VP and GBI. The following tests will be used to analyze the experience of caries: *t* of “Student” and of chi-square. The significance level will be set at 5%.

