**Methods:**

This study was designed as a randomized, double-blind, parallel clinical trial involving 100 pairs of mothers and children (6–12 years old). The mothers and children will be randomly allocated to the control group (*n* = 50 pairs), who will receive a single visit conventional oral health education, or to the experimental group (*n* = 50 pairs), who will receive both a single visit conventional oral health education and educational videos through WhatsApp Messenger, twice a week. Before randomization of the groups and after the intervention, pairs will be evaluated regarding to plaque index (VPI), gingival bleeding index (GBI), and number of decayed, missing and filled permanent or primary teeth (DMF-T) modified by the inclusion of active non-cavitated carious lesions (Nyvad criteria). Socioeconomic data, dental history, and oral health literacy will obtained using questionnaires (Oral Health Literacy Assessment Task for Paediatric Dentistry; BOHLAT-P). Chi-square, Student’s *t*-test, paired Student’s *t*-test, Mann-Whitney, and Friedman tests will be used with a 5% significance level.

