Dental studies have achieved good results using an oral health education tool to inform and motivate adolescents [22, 23]. A digital medium with widespread use in Brazil is WhatsApp Messenger, which is an application that allows rapid interaction through texts, images, voice and video calls [24]. Consequently, this application may be an effective social media tool for disseminating health education [25]. In this context, a 2016 survey conducted in Brazil showed that 76% of users who searched the Internet made continuous use of WhatsApp, and this percentage is one of the highest worldwide, second only to South Africa [26]. However, the efficacy of using WhatsApp to promote oral health education for mothers and children has not yet been elucidated in the literature.

The objective of this parallel, double-blind, and randomized clinical trial is to compare the influence of conventional education promoting oral health, versus that of conventional education plus the WhatsApp digital platform, in controlling dental biofilm and caries in mother-child pairs. Mothers and their children (age 6–12 years) will be evaluated through a self-administered questionnaire on oral hygiene habits, and through the Oral Health Literacy Assessment Task for Paediatric Dentistry (BOHLAT-P). In addition, clinical parameters of the mother-child pairs (including the visible plaque index [VPI], gingival bleeding index [GBI], number of decayed, missing, and filled deciduous teeth [dmft], and the numbers of decayed, missing, and filled permanent teeth [DMFT modified by the inclusion of active non-cavitated carious lesions]) will be considered in the assessment. We hypothesized that mother-child pairs randomized to the experimental group would exhibit greater improvements in oral hygiene behavior and health outcomes when compared with the control group during follow-up assessments at 1, 6, and 12 months.

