### Interventions

The following study groups will be created in parallel to evaluate the proposed intervention. (1) Control group: Both mothers and children will undergo clinical examination, prophylaxis, topical fluoride application, and oral hygiene guidance on a single dental office visit. The pairs will receive an oral hygiene in-person orientation session that will take about 30 min regarding to oral health, gingival health, sugar intake, fluoride importance in prevention of dental caries, and oral hygiene habits, complemented with illustrative resources.

(2) Experimental group: Both mothers and children will receive clinical examinations, prophylaxis, topical fluoride application, and oral hygiene guidance on a dental office visit. Additionally, the digital platform WhatsApp Messenger (Mountain View, California) will be used to provide educational videos to the mother-child pairs, twice per week (Tuesday and Thursday) at 7 PM over a period of 4 weeks. A WhatsApp video presenting a story on oral health, along with a reminder to perform their oral hygiene routine (toothbrushing and flossing) will be sent to the mother-child pairs in the experimental group. Topics including oral hygiene, dental biofilms, white spot lesions, dental caries, and the importance of dental appointments will be covered. Videos were validated by educators and a group mother-child pairs who evaluated the quality of the animated videos and understanding of the topics covered according to Marinho et al. [27].

At the end of 4 weeks (T1), 6 months (T2), and 12 months (T3), the mother-child pairs will undergo follow-up clinical evaluations at FORP/USP. If needed, dental treatment will be performed by a research team at the same institution.

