### Outcome measurements

Measurements will be taken at baseline, post-intervention (i.e., 30 days after completion of the intervention), and at the 6-month and 12-month follow-up points. All follow-up assessments will be conducted by a researcher blinded to the group allocation of the participants.

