### Measurement of primary outcomes

The primary outcome is defined as the effectiveness of educational videos via WhatsApp Messenger for controlling dental biofilm and dental caries in mother-child pairs. This outcome will be achieved by evaluating the VPI, GBI, and dmft indexes for deciduous teeth, and the DMFT for permanent dentition. Dental caries will be evaluated using the Nyvad Criteria to assess severity and activity of carious lesions. These results will be compared with those of the control group throughout the follow-up.

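### The VPI and GBI tests use no stated baseline adjustment between arms, which costs precision, and the within-arm Friedman tests do not address the intervention

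*Protocol article*

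**What the plan says.** The Statistical analyses section of the protocol article assigns the tests for VPI and GBI: "the Mann-Whitney test will be used to compare the inter-group differences, and Friedman test will be used to calculate intra-group differences". The significance level is 5%. The abstract lists the same two tests and adds a paired t-test, which is also a within-arm test. Neither place names an analysis of covariance, a mixed model, a change score or an arm-by-visit term.

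Four other statements bear on this choice:

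- **Baseline is available.** The abstract says: "Before randomization of the groups and after the intervention, pairs will be evaluated regarding to plaque index (VPI), gingival bleeding index (GBI"). The section on outcome measurements gives the schedule: "Measurements will be taken at baseline, post-intervention (i.e., 30 days after completion of the intervention), and at the 6-month and 12-month follow-up points".
- **The hypothesis concerns improvement relative to control.** The Background expects that the experimental pairs "would exhibit greater improvements in oral hygiene behavior and health outcomes when compared with the control group", and it names three follow-up points: 1, 6 and 12 months.
- **VPI and GBI are primary.** Of the primary outcome the article says: "This outcome will be achieved by evaluating the VPI, GBI, and dmft indexes for deciduous teeth, and the DMFT for permanent dentition". The results are to be compared with those of the control group over follow-up.
- **Both arms get active care at the office visit.** For the control arm: "Both mothers and children will undergo clinical examination, prophylaxis, topical fluoride application, and oral hygiene guidance on a single dental office visit". The experimental arm receives the same, plus the videos.

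**The concern.** A hypothesis about improvement starts from baseline, yet the only stated tests that clearly involve the baseline values are the within-arm ones. The between-arm test is described only as comparing differences between groups. If that means follow-up values, the information in the baseline measurement is unused. If it means changes, baseline is used, but in a way that can be less efficient than no adjustment at all.

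The within-arm tests answer a different question. Plaque and bleeding can be expected to fall in both arms after cleaning, fluoride and guidance, whether or not the videos work. A Friedman result therefore shows change over time under each arm's whole package of care, not the effect of adding videos. The section does not mark these results as descriptive.

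At stake are the precision of the comparison for two primary indexes, and clarity about which result carries the conclusion.

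**Working it through.** **Inputs from the protocol article.** Alpha 5% and power 80%, giving 44 pairs per arm (Sample size and power calculation); 50 pairs per arm planned (abstract).

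**Assumptions.** Two-sided testing, normal data, equal variances, and a correlation r between baseline and follow-up. The article gives no value for r, so a range of 0.1 to 0.7 is shown.

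**Step 1. The plan's own figure.** The figure of 44 cannot be reproduced, because no endpoint, effect or standard deviation is stated. It can only be solved backwards:

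d = √(2/44) × (1.960 + 0.842) = 0.2132 × 2.802 = 0.597.

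The t-test version gives 0.604. So 44 per arm corresponds to d of about 0.60. Applying this to VPI or GBI is an assumption.

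**Step 2. Effect of baseline adjustment.** Adjustment multiplies the residual variance by 1 − r². Power is approximately Φ( d√(n/2) / √(1 − r²) − 1.960 ).

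At n = 44, d√22 = 2.802. At n = 50, d√25 = 2.987.

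| r | 1 − r² | Power, 44 per arm | Power, 50 per arm, no dropout |
|---|---|---|---|
| unadjusted | 1 | 80% | 85% |
| 0.1 | 0.99 | 80% | – |
| 0.2 | 0.96 | 82% | – |
| 0.3 | 0.91 | 84% | 88% |
| 0.5 | 0.75 | 90% | 93% |
| 0.7 | 0.51 | 98% | 99% |

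Worked row, r = 0.5, n = 44: 2.802/0.866 = 3.235; 3.235 − 1.960 = 1.275; Φ = 0.899.

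Put as sample size, 44/(1 − r²) gives 48, 59 and 86 unadjusted pairs per arm as the equivalent of 44 adjusted pairs at r = 0.3, 0.5 and 0.7.

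**Step 3. The tests actually named.** A simulation (4,000 runs per setting, normal data, 44 per arm, d = 0.597) gave:

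| Analysis | r = 0.3 | r = 0.5 | r = 0.7 |
|---|---|---|---|
| Mann-Whitney on follow-up value | 77% | 77% | 77% |
| Mann-Whitney on change | 61% | 77% | 93% |
| ANCOVA | 81% | 89% | 97% |

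Type I error was about 5% for all three. The two readings of the between-arm test therefore differ in power, and adjustment exceeds both at each r simulated. The variance of a change is 2(1 − r) times that of a single value, so below r = 0.5 a change score is noisier than the follow-up value alone.

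**Step 4. What the Friedman tests can show.** With identical true improvement in both arms (four visits, 44 per arm, between-visit correlation 0.5), exactly one arm's Friedman test was significant in 10% of simulated trials with no improvement, 30% at 0.2 SD, 48% at 0.3 SD, 47% at 0.4 SD and 26% at 0.5 SD. The between-arm Mann-Whitney stayed at about 5% throughout. These figures matter only if significance in one arm alone were read as an effect.

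**The case against.** The strongest reply is that the plan is valid as it stands. A between-arm test is specified, the primary outcome is framed as a comparison with control, and under randomization an unadjusted Mann-Whitney test keeps its 5% level. Chance baseline imbalance is already allowed for in that error rate. A rank test is also a sensible choice for bounded percentages of sites. All of this stands, and it limits the point to precision and clarity.

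The power gain rests on inputs that the article does not give. The source study is described as measuring a game for delivering oral health knowledge, so d of about 0.60 may not apply to plaque or bleeding. Prophylaxis at the first visit could weaken the link between baseline and later values, and at r of 0.1–0.2 the gain is close to nil. At the planned 50 per arm with no dropout, unadjusted power is already 85%. This also stands, and is why a range is given.

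Stronger readings are tempting but unsupported:

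- A reader might infer that baseline is certainly ignored between arms. The wording leaves room for change scores, so the defect is that it does not say.
- A reader might infer that the investigators will claim efficacy from a Friedman test significant in one arm only. No section says so.
- A reader might infer that mothers and children will be pooled as independent records. The sample size is counted in pairs and numbers are assigned per pair; pooling is proposed nowhere.
- A reader might infer that the rank test cannot yield an estimate. It can be accompanied by a Hodges-Lehmann shift with a confidence interval.

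**Conclusion.** The point holds as a cheap and worthwhile improvement, not as an error that invalidates the trial. The section fixes the tests for two primary indexes, names no baseline-adjusted between-arm comparison, and leaves open whether values or changes are compared. Given d of about 0.60, 44 per arm and normal data, the gain from adjustment runs from negligible at r = 0.1 to about 18 percentage points at r = 0.7 (80% to 98%). At 50 per arm with no dropout it is about 3 to 14 points over r = 0.3 to 0.7 (85% to 88%, and 85% to 99%). Both d and r are assumptions.

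The conclusion on Friedman needs no such assumptions: a within-arm test does not test the added effect of the videos, and the text should say so. The documents do not support calling the planned between-arm test biased or its error rate inflated.

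**What to change.** Amend the Statistical analyses section as follows:

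1. Make the main VPI and GBI comparison a baseline-adjusted between-arm analysis: either ANCOVA at each follow-up, or a mixed model over the 1-, 6- and 12-month values with arm, visit, arm-by-visit and the baseline value.
2. Run it separately for mothers and for children, and report the adjusted difference with its 95% CI at each stated follow-up.
3. Keep Mann-Whitney as a sensitivity analysis, because the indexes are bounded percentages, and state whether it is applied to follow-up values or to changes.
4. Label the Friedman results, and any paired within-arm test of these indexes, as descriptive and carrying no conclusion about the intervention.

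The cost is a change of wording, and possibly software other than the named package. No new data or visits are needed. The downside is a model assumption, which the rank-based sensitivity analysis covers.

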### Sample size and power calculation

To calculate the sample size, we used the study by Zolfaghari et al. [10], which measured the efficacy of a game for delivering oral health knowledge to children and mothers. Considering an alpha value of 5% and a test power of 80%, the sample calculation requirement was 44 mother-child pairs per group (control and experimental).

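### As named, the VPI and GBI tests make no use of the earlier values of people who miss a visit, although the video content could make attendance differ by arm

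*Protocol article*

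**What the plan says.** The Statistical analyses section of the protocol article fixes the tests for VPI and GBI: "the Mann-Whitney test will be used to compare the inter-group differences, and Friedman test will be used to calculate intra-group differences". Caries experience is to be tested with Student's t and chi-square. The section states no analysis set and no rule for absent values.

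The indices are recorded at baseline and at three follow-up examinations (T1 at about one month, T2 at 6 months, T3 at 12 months), all at the research clinic. An index value therefore exists only for a pair that attends.

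The Interventions section lists the video topics, which end with "dental caries, and the importance of dental appointments will be covered". Only the experimental arm receives the videos. The topics listed for the in-person session do not include appointments. Visits to the dentist are also among the secondary outcomes.

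Strategies for study retention gives both arms the same text reminders and adds: "In the case of no attendance, calls will be made to the participant (mother) to reschedule the missed dental evaluation".

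The abstract plans 100 pairs, 50 per arm. Sample size and power calculation requires 44 per arm at 5% alpha and 80% power.

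**The concern.** The intervention promotes a behaviour, keeping dental appointments, that also decides who is measured. If the message works, more experimental families than control families return at 6 and 12 months. If the families lost are also those with more plaque and bleeding, the control families still attending are a cleaner-mouthed selection, and the between-arm difference shrinks.

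The named tests cannot correct for this by themselves. Mann-Whitney at a visit uses the values recorded at that visit. Friedman drops anyone without all four examinations. The baseline, T1 and T2 values of a pair absent at T3 are collected but not used in the T3 comparison. T1, T2, T3 and the Friedman analysis may then each describe a different subset, so a fading effect would be hard to tell from selective loss.

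**Working it through.** **Inputs from the article.** 44 pairs per arm required, 5% alpha, 80% power; 50 pairs per arm planned; four examinations. No effect size, SD, dropout rate or correlation between visits is given.

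**Inputs assumed.** Two-sided test; correlation 0.6 between any two visits; one index value per pair; attendance rates as shown below.

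**1. The plan's own figure.** With no effect size stated, 44 can only be solved backwards (normal approximation):

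d = (1.960 + 0.842) × √(2/44) = 0.597, about 0.60 SD.

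Forwards, d = 0.60 gives 44 per arm. Planning 50 leaves room for 1 − 44/50 = 12% loss. That protects numbers, not comparability.

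**2. Bias among attenders at T3.** Trials were simulated with 50 per arm, a true difference of 0.60 SD at every follow-up, and dropout before T3 depending on the T2 value through a logistic model (log odds ratio 0.5 to 1.5 per SD, worse hygiene more likely to be lost).

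| Loss, control / experimental | Difference among attenders | Mann-Whitney power |
|---|---|---|
| none (full data) | 0.60 SD | about 83% |
| 12% / 12% | 0.60 SD | about 79% |
| 20% / 8% | 0.53 to 0.56 SD | 68 to 71% |
| 30% / 10% | 0.48 to 0.54 SD | 55 to 64% |

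An estimator that predicts missing T3 values from baseline, T1 and T2 returns about 0.60 SD in all these settings. Its sampling error is about 0.17 SD, against about 0.21 SD for attenders only.

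**3. How much of the power loss is selection.** With the same losses completely at random, power is about 77% (20%/8%) and 73% (30%/10%). So at 20%/8% roughly 83 − 77 = 6 points are fewer people, and a further 77 − 71 = 6 to 77 − 68 = 9 points come from selection. At 30%/10% the split is 83 − 73 = 10 points, and then 73 − 64 = 9 to 73 − 55 = 18 points.

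**4. A second model.** Let a latent tendency to attend have correlation ρ with better hygiene. With attendance p, the mean index among attenders is shifted by −ρ·φ(c)/p, where c = Φ⁻¹(1 − p). For 94% attendance (experimental), 82% (control) and ρ = 0.3:

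- experimental: −0.3 × 0.119/0.94 = −0.038
- control: −0.3 × 0.262/0.82 = −0.096
- bias: −0.038 − (−0.096) = 0.058 SD against the videos, about 10% of 0.597

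Over 94%/82% to 95%/65% and ρ = 0.2 to 0.5, the bias is 0.04 to 0.23 SD. It is zero if attendance is equal, and zero if ρ = 0.

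**5. Direction.** With 20%/8% loss and the opposite sign (log odds ratio −1, cleaner-mouthed families lost), the attenders' difference is about 0.66 SD, which exaggerates the benefit.

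**6. Dropout that depends on the unseen T3 value.** At 20%/8% loss the estimator using earlier visits gives 0.52 to 0.54 SD (log odds ratio 1 to 1.5), against about 0.48 SD for attenders only at the stronger dependence. It is closer to 0.60 but not free of bias.

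**7. Friedman.** If each of three follow-up visits is missed independently with probability p, the share with all four is (1 − p)³: 0.95³ = 86% (43 of 50) and 0.88³ = 68% (34 of 50).

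**The case against.** The strongest reply is that the article names tests but never says that only attenders will be analysed. Mann-Whitney can be run on imputed data, and the analysis set and missing-data method are commonly left to a full protocol or SAP that is not shown. That stands as far as it goes: the silence is not the point here. A reader might infer that the plan commits to an attenders-only analysis, and the document does not say so. What it does fix is a pair of tests that, as named, make no use of earlier visits, in a four-visit design whose intervention touches attendance.

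A reader might also infer that the T2 and T3 comparisons are biased towards no effect. The documents do not support that. Bias needs attendance that is both unequal and related to oral hygiene. No data on either are given, and the direction can reverse (step 5). Appointments are one of several video topics, the videos run for four weeks, and both arms get the same reminders and calls. Dental treatment is offered if needed without distinction by arm. All of this lowers the risk without removing it.

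Three further points stand. At 20%/8% loss the bias of 0.04 to 0.07 SD is at most about a third of the standard error. Friedman is used only within groups, so its loss of incomplete pairs does not bias the between-arm contrast. The full recovery in step 2 follows from simulating dropout that depends on an observed value. A set restricted to pairs with at least one follow-up examination can still be shaped by attendance, though less than the T3 attenders alone.

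**Conclusion.** The point holds as a cheap improvement, not as a demonstrated error. The named tests leave earlier values unused, and the plan's own video content gives a specific reason why attendance could differ by arm. If it does, and if attendance is related to hygiene, comparing attenders can mislead in either direction.

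Under assumed losses of 20%/8% to 30%/10%, related to the T2 value, a true 0.60 SD is estimated at about 0.48 to 0.56 SD. Part of the accompanying loss of power is simply fewer people. These sizes rest on assumed dropout rates and correlations, and on an effect of 0.60 SD solved backwards from the sample size. Equal losses give no bias.

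**What to change.** In Statistical analyses:

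- Make the between-arm analysis of VPI and GBI a likelihood-based repeated-measures (mixed) model with arm, visit, arm-by-visit and the baseline index, fitted to every randomised pair with any follow-up examination.
- Keep Friedman as descriptive only.
- Report attendance by arm at T1, T2 and T3.
- Add one sensitivity analysis that shifts the missing T3 values, because the model removes the bias fully only if data are missing at random.

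Cost: analysis-plan wording, a little more analysis work and possibly other software. No new data or participants are needed, since baseline, T1 and T2 values are already collected. The downside is reliance on model assumptions, including missing at random, which the sensitivity analysis probes.
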